## Abstract

**Background:**

Preterm birth is a global problem, with a prevalence of 8 to 12% depending on location. Several large trials and systematic reviews have shown progestogens to be effective in preventing or delaying preterm birth in selected high risk women with a singleton pregnancy (including those with a short cervix or previous preterm birth). Although an improvement in short term neonatal outcomes has been shown in some trials these have not consistently been confirmed in meta-analyses. Additionally data on longer term outcomes is limited to a single trial where no difference in outcomes was demonstrated at four years of age of the child, despite those in the “progesterone” group having a lower incidence of preterm birth.

**Methods/Design:**

The OPPTIMUM study is a double blind randomized placebo controlled trial to determine whether progesterone prophylaxis to prevent preterm birth has long term neonatal or infant benefit. Specifically it will study whether, in women with singleton pregnancy and at high risk of preterm labour, prophylactic vaginal natural progesterone, 200 mg daily from 22 – 34 weeks gestation, compared to placebo, improves obstetric outcome by lengthening pregnancy thus reducing the incidence of preterm delivery (before 34 weeks), improves neonatal outcome by reducing a composite of death and major morbidity, and leads to improved childhood cognitive and neurosensory outcomes at two years of age. Recruitment began in 2009 and is scheduled to close in Spring 2013. As of May 2012, over 800 women had been randomized in 60 sites.

**Discussion:**

OPPTIMUM will provide further evidence on the effectiveness of vaginal progesterone for prevention of preterm birth and improvement of neonatal outcomes in selected groups of women with singleton pregnancy at high risk of preterm birth. Additionally it will determine whether any reduction in the incidence of preterm birth is accompanied by improved childhood outcome.

**Trial registration:**

ISRCTN14568373

## Background, including rationale and any previous systematic review(s)

Preterm birth is a global problem, with a prevalence of 8 to 12% depending on location [1]. Around 75% of preterm birth follows spontaneous preterm labour, sometimes preceded by preterm premature membrane rupture [2]. Babies born preterm are at increased risk of a variety of adverse short term (neonatal) and long term complications, including neurodevelopmental disability. Women with a previous preterm birth (especially those women who delivered before 34 weeks following spontaneous preterm labour), women with a short cervix in early pregnancy [3], and women with a previous cone biopsy or laser loop excision to the cervix [4] are at all at increased risk of spontaneous preterm birth.

Several large trials and meta-analyses have shown progesterone to be effective in preventing or delaying preterm birth in selected high risk women (short cervix or previous preterm birth) with singleton pregnancy [5-11]. There is data that both intramuscular 17 hydroxyprogesterone caproate and vaginal progesterone are effective in preventing preterm birth. OPPTIMUM likewise is investigating the efficacy of progesterone in women at elevated risk of preterm birth, but will crucially address longer term childhood developmental outcomes.

Although an improvement in short term neonatal outcomes has been shown in some trials [6-8] these have not consistently been confirmed in meta-analyses [9,10]. Data on longer term outcomes in singletons is limited to follow up of babies of women in the Meis trial, where 80% of babies were assessed by questionnaire at a mean age of four years. No differences in childhood outcomes were demonstrated, despite the progesterone group having a lower incidence of preterm birth [12].

The mechanisms of action of progesterone are somewhat uncertain although a direct inhibitory effect on the processes of parturition seem likely [13]. Additionally progesterone could exert anti-inflammatory properties [13] and/or direct CNS protective effects [14], which could help to reduce the risk or severity of long term neonatal problems.

If the prevention of preterm birth is accompanied by a reduction in the complications of prematurity, then *in utero* progesterone should be predicted to have long term beneficial effects. Harmful long term effects are however also possible. Although direct teratogenic effects of progesterone are unlikely, there could be adverse effects of keeping the fetus in utero in a compromised intrauterine environment where infection or inflammation is present. Caution is therefore warranted before progesterone use becomes widespread, particularly since drugs (including antibiotics and estrogens) thought to be beneficial in women at risk of preterm birth have now been demonstrated to have long term adverse effects [15-17].

The OPPTIMUM study is designed to determine whether progesterone prophylaxis to prevent preterm birth has long term neonatal or childhood benefit. Specifically it will study whether, in women at elevated risk of preterm labour, prophylactic vaginal natural progesterone, 200 mg (compared to placebo), daily from 22 – 24 weeks up to 34 weeks gestation, improves obstetric outcome by lengthening pregnancy thus reducing the incidence of preterm delivery (before 34 weeks), improves neonatal outcome by reducing a composite of death and major morbidity and leads to improved childhood cognitive and neurosensory outcomes at two years of age.

The OPPTIMUM study began recruiting in January 2009. Since then, one large, and several other smaller studies have reported the effect of progesterone, either as vaginal progesterone or as intramuscular 17 hydroxyprogesteronecaproate. None fully addresses the crucial question regarding long term outcome (childhood development at 2 years). Additionally, we note that the US Food and Drug Administration (FDA) has indicated that long term childhood outcome data are required to determine the clinical benefits and risks of 17 hydroxyprogesteronecaproate for the prevention of preterm birth in women with a previous preterm birth._._^a^ An FDA panel also recently ruled that data supplied on vaginal progesterone gel “do not [yet] support the efficacy of progesterone gel compared with placebo in reducing the risk of preterm births before 33 completed weeks of gestation among women with a short cervical length”.^b^ We believe that OPPTIMUM will address these important evidence gaps about the efficacy of vaginal progesterone and any childhood effects of progestogens in general.

## Methods

### Aim(s)

The aim of the OPPTIMUM study is to determine whether, in women at high risk of preterm labour, prophylactic vaginal natural progesterone, 200 mg daily from 22 – 34 weeks gestation, compared to placebo:

• Improves obstetric outcome by reducing the incidence of preterm delivery (before 34 weeks gestation).

• Improves neonatal outcome by reducing a composite of death and major morbidity.

• Leads to improved childhood cognitive and neurosensory outcomes at two years.

### Centre(s)

More than 60 hospitals, principally in the UK.

### Design

Double blind randomized placebo controlled trial. The study is in two phases, a screening phase and a treatment phase.

### Inclusion and exclusion criteria

#### Screening phase inclusion criteria

High risk for preterm birth (as indicated by AT LEAST ONE of the criteria i-iv) and ALL of the criteria v-vii:

i. History of previous PTB/second trimester loss (≥16 weeks or ≤37 weeks gestation)

ii. Previous preterm premature rupture of the fetal membranes (≤ 37 weeks gestation)

iii. Short cervical length (≤ 25 mm) on ultrasound at 18–0 -24 + 0 weeks gestation

iv. Any cervical procedure to treat abnormal smears i.e. large loop excision, laser conisation, cold knife conisation or radical diathermy

v. Gestation established by scan at ≤ 16 weeks to ensure that the estimated date of delivery is accurate or the consultant must be confident that the gestation dates are accurate.

vi. Signed Consent form

vii. 16 years of age or older.

#### Treatment phase inclusion criteria

• All women fulfilling the inclusion criteria for the screening phase and who also have a positive screening (fFN) test at 22 + 0 weeks, will be eligible for the main (treatment) phase of the study – these women are subsequently referred to as the “fFN positive” group.

• Additionally, in September 2010, those who have a previous spontaneous labour resulting in a preterm birth ≤ 34 weeks gestation (delivery by any mode) or a short cervix in index pregnancy, defined as cervical length ≤ 25 mm at 18–0 -24 + 0 weeks gestation also became eligible for randomisation even with a negative fFN test. These women are subsequently referred to as the “fFN negative” group

### Exclusion criteria

• Known significant congenital structural or chromosomal fetal anomaly

• Known sensitivity or listed contraindication to progesterone (known allergy or hypersensitivity to progesterone, severe hepatic dysfunction, undiagnosed vaginal bleeding, mammary or genital tract carcinoma, thrombophlebitis, thromboembolic disorders, cerebral haemorrhage, porphyria) or intolerance to progesterone or excipient (including peanut allergy prior to February 2011 given that peanut oil was the excipient in doses issued to participants until November 2010)

• Suspected or proven rupture of the fetal membranes at the time of recruitment

• Multiple pregnancy

Prescription or ingestion of medications known to interact with progesterone (e.g. Bromocriptine, Rifamycin, Ketoconazole or Ciclosporin)

• Women currently prescribed progesterone or who have taken progesterone beyond 18 weeks gestation.

*Intervention(s)* Progesterone (Utrogestan) 200 mg soft capsules or placebo will to be inserted once daily vaginally at bedtime from 22^+0^ - 24^+0^ up to 34^+0^ weeks gestation.

### Randomisation

Randomisation will be carried out online via the web portal or via telephone to the central randomisation facility based at the Robertson Centre for Biostatistics, at the Glasgow Clinical Trials Unit, University of Glasgow.

### Concealment of allocation

Concealment of allocation will be achieved by randomising participants to active or placebo capsules. Placebo capsules will appear identical to active treatment. The outcomes will be measured blind to the allocation.

### Primary and any secondary endpoint(s)

Primary endpoints:

• Obstetric: delivery <34 completed weeks of gestation (Yes/No), (<34 + 0 weeks: outcome of the treatment phase)

• Neonatal: a composite of death or two markers of neonatal morbidity – bronchopulmonary dysplasia in children born at <32 weeks of gestation and brain injury on cerebral ultrasound.

• Childhood: The Bayley III cognitive scale standardised score at two years of chronological age (with an aim to test between 22 months to 26 months - as this is age-standardised all assessments will be valid)

Secondary endpoints:

• Gestation at delivery

• Fetal or neonatal/infant death after trial entry up to 2 years of age [18].

• Incidence of the individual components of the primary neonatal outcome

• Incidence of other major neonatal complications:

• Level of care days, which includes: days of respiratory support, (Either mechanical ventilation or CPAP) and days of oxygen therapy.

• Surfactant administration

• Necrotising enterocolitis, (medical or surgical treatment of confirmed cases)

• Number of discrete episodes of bloodstream or CNS infection (positive blood [19] or CSF culture)

• Daily level of care [20].

• Composite outcome of death or moderate/severe neurodevelopmental impairment at two years of age, defined as per national recommendations [21].

• Individual components of the disability definition and non-neurological disability as defined [21].

• Strengths and difficulties questionnaire (http://www.sdqinfo.com/)

• Score on the PARCA-r (parent assessment of child abilities revised).

• Women’s perceptions of their treatment.

• Maternal and child adverse events (e.g. operative delivery).

### Side-effects reporting and quantification (e.g, WHO scale)

Participants are instructed to contact their Investigator at any time after consenting to join the trial if any symptoms or side effects develop. In the case of any events the Investigator should initiate the appropriate treatment according to their medical judgment. All adverse events (AEs) and Serious Adverse Events (SAE) that occur after being randomized to treatment must be recorded in detail in the patient notes. SAEs occurring in mother or baby from the time a participant is randomised until 30 days after stopping taking study treatment/placebo or until 28 days after delivery (whichever is the later) should be reported to the co-sponsors using the trial documentation. The standard definition of a serious adverse event will be used [22]. This is any event that: results in death; is life threatening (i.e. the subject was at risk of death at the time of the event; it does not refer to an event which hypothetically might have caused death if it were more severe); requires hospitalisation or prolongation of existing hospitalisation; results in persistent or significant disability or incapacity; is a congenital anomaly or birth defect. Hospitalisations for treatment planned prior to randomisation and hospitalisation for elective treatment of a pre-existing condition will not be considered as an SAE, nor, for the purposes of this study, will the following events: miscarriage, preterm labour / suspected preterm labour, premature rupture of membranes (PROM) / suspected PROM, preterm delivery, preterm delivery in maternal interest, preterm delivery in fetal interest, hospitalisation for pregnancy induced hypertension, hospitalisation for “maternal discomfort”, hospitalisation for “rest”, hospitalisation for “observation” or “monitoring” for which the women are admitted for a period of less than 12 hours; normal” childhood illnesses (including infectious diseases and minor injuries) and complications arising from prematurity.

### Statistical analysis plan, including sample size and power calculations

At the commencement of the study in 2008, we planned to recruit 750 women in the “fFN positive” group. We estimated that such a sample size would provide 80 – 95% power at the 5% level of significance for the primary obstetric outcome, 80% power for the neonatal outcome and 93% power for the childhood outcome (although further dilution of the latter was anticipated after incorporation of the deaths in a two stage statistical model – see below).

In 2010, the study was expanded to allow randomisation of women in the “fFN negative” group after analysis of preliminary (blinded) data in July 2010, together with the result of an HTA funded systematic review on screening for preterm birth [23] showed that our initial selection strategy erroneously missed women at medium to high risk of preterm birth. This change was endorsed by the Trial Steering committee, the MHRA, the ethics committee, and by the funder. The inclusion of women at a lower risk of the primary outcomes necessitated an increase in the sample size. The minimum new sample size is anticipated to be in the order of 1125 (375 fFN positive and 750 fFN negative women), but the proportions of each will dictate the exact sample size, as it is anticipated that at least 2 fFN negative women are required to achieve the event rate predicted in 1 fFN positive woman. Workings for the sample size calculation for the fFN positive group alone, and for the revised combined group of fFN positive and fFN negative women are shown in the Appendix.

### Type of analysis (e.g. intention to treat) and statistical tests

All primary efficacy analyses are carried out on the intention to treat population (ITT). Safety analyses are carried out on the safety population (those who initiated on what study medication they received). Primary analyses are repeated in an exploratory manner on the per protocol population (including [i] compliance within an acceptable range and [ii] fulfilment of inclusion and exclusion criteria).

#### Obstetric outcome

The primary obstetric outcome is delivery or fetal death before 34 completed weeks of gestation based on ultrasound (based on the projected date of delivery estimated from scan in the first trimester). The following null hypothesis will be tested: ‘There is no difference in the incidence of delivery or fetal death before 34 completed weeks of gestation between the group treated with 200 mg / day progesterone and the group treated with placebo from week 22–24 to week 34 of gestation or earlier delivery’.

The outcome is compared between the treatment groups using a logistic regression model including treatment and previous pregnancy of at least 14 weeks. The hypothesis will be tested with a likelihood ratio test.

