#### Neonatal outcome

The primary neonatal outcome is a binary outcome indicating whether one of the following has occurred:

• Death

• Brain injury (defined as any intraventricular haemorrhage (IVH) (excludes subependymal haemorrhages), parenchymal cystic or haemorrhagic lesion or persistent ventriculomegaly (VI >97th percentile)

• Severe chronic lung disease (defined as need for ≥30% oxygen and/or positive pressure (positive pressure ventilation or nasal continuous positive airway pressure) at 36 weeks post menstrual age or discharge, which ever comes first).

The following null hypothesis will be tested: ‘There is no difference in the combined incidence of neonatal death, brain injury or severe chronic lung disease between the group treated with 200 mg / day progesterone and the group treated with placebo from week 22–24 to week 34 or earlier delivery’ This outcome is also compared between the treatment groups using a logistic regression model including treatment and previous pregnancy of at least 14 weeks. The hypothesis will be tested with a likelihood ratio test.

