### Planned subgroup analyses

In order to determine whether a reduced or improved response to progesterone can be predicted, subgroups of the ITT population will be formed according to the following factors:

• reason for risk of preterm delivery (spontaneous preterm birth yes / no and any preterm birth yes / no)

• previous pregnancy of at least 14 weeks (yes / no)

• cervical length at 18–24 weeks gestation (≤25 mm / >25 mm and ≤15 mm / >15 mm)

• chorioamnionitis diagnosed on pathology (yes / no)

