## Appendix

### Sample size calculations

#### Original sample size calculation based on data in the literature on the “fFN +” group

A sample size of 750 (375 per group) gives adequate statistical power to detect clinically important and plausible differences in the three primary measures of outcome. All these power calculations allow for loss to follow up rates and compliance. Delivery <34 weeks on placebo is expected to be 40% (data from an untreated high risk UK population with a positive fFN test at 22 weeks [27] and 27% on progesterone consistent with the odds ratio of 0.45 for the overall PTB with any progestational agent in the most recent systematic review [28]. With 750 randomised, the study will have 95% power at a 5% level of significance to detect such a reduction from 40% to 27% using a two-sided binomial test. For a more modest reduction from 40% to 30% (odds ratio 0.64) the study would still have 80% power. For the neonatal outcome, the Meis study found 7.2% died, 14.6% had CLD and 5.2% had IVH on placebo, compared to 4.6% death, 8.6% CLD and 1.3% IVH on progesterone [4]. Our neonatal primary outcome is a composite of these and also includes non-haemorrhagic brain injuries. With n = 750 randomised, the OPPTIMUM study would have 80% power at a 5% level of significance to detect a difference in this composite outcome of death, brain damage, or chronic lung disease from 20 to 12%, using a binomial test.

The childhood developmental outcome at 2 years will be assessed using the Bayley III Cognitive Scale which correlates well with later IQ. With 750 randomised, the study will have 93% power at a 5% level of significance to detect a difference in means equivalent to 0.25 of a standard deviations, using a two sample two sided *t*-test. Based on previous work [29], we estimate the standard deviation will be about 15 points, enabling us to detect a difference of 4 points in the Bayley Score. In clinical terms, a difference of 4 points is small, thus the power of the study to detect larger, more clinically significant differences, is high. We have powered this outcome at over 90% to make some allowance for a possible dilution of the power due to incorporating the deaths (using a two stage statistical model).

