#### The revised sample size calculation below, based on blinded data (as of April 2011) and inclusion of the "fFN"- group is around 1250 participants

**Obstetric outcome** (delivery <34 weeks).

The table below gives the estimated power for three combinations of sample size (all 1:2 fFN+/fFN- groups, assuming 375:750 (total 1125), 400:800 (total 1200) and 425:850 (total 1275) assuming (fFN+, fFN-) event rates (delivery < 34 weeks) of (40%, 10%), (45%, 13%), and (45%, 15%). All calculations assume a relative treatment effect of 32.5%.

The justification for these combinations is as follows:

1. The 40% untreated rate is as per the original assumption. We have looked at the blinded (aggregated) event rate for the first 67 women randomised in OPPTIMUM (ignoring any possible bias created by recording the early births before later births in the most recently randomised). For the fFN + group, 29/67 (43%, 95% exact confidence interval 31% to 56%) had delivered at <34 weeks. The blinded event rate according to the assumed 40% untreated rate with a 27% treated rate (32.5% relative reduction) would be 33.5%. Although the numbers are relatively small, there appears to be a higher event rate than anticipated, which would be consistent with having selected a higher risk and hence scarcer subset than we planned for). An overall blinded rate of 43% could comprise an untreated rate of 52% and a treated rate of 35%. We assume conservatively that the baseline event rate in the untreated fFN + group is 45%.

2. For the fFN- group women data on the first 24 women suggested that 8/24 (33%, exact 95% confidence interval 16% to 55%) had delivered early. As indicated above, this percentage is likely to be inflated since we record the early deliveries before observing the term deliveries. However, fortunately, we also had followed up those who were not randomised (by definition, all of whom had a negative fFN test) into OPPTIMUM from the start. Of the 398 followed, 32 have had a delivery <34 weeks. We know that 57% of these 398 would have been eligible for the trial (short cervix < 25 mm), and the epidemiology indicates that it is very unlikely to give birth <34 weeks with none of the classic risk factors. So we conservatively estimate that around 13% (i.e. around 29/225, exact confidence interval 9% to 18%) of those recruited into the fFN- group, based on OPPTIMUM data, will have a delivery <34 weeks.

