There are no data yet on this outcome within OPPTIMUM. In the original calculation we assumed that the difference in mean Bayley score would be 4 units with a common standard deviation of 15 units. It is more difficult to assess the power convincingly with a mixture of fFN + and fFN- women on a continuous outcome such as the Bayley Score, since the power calculation requires assumptions about not just the anticipated treatment effect but also the assumed variability via the standard deviation. If we assume the same 4 unit difference in the fFN + and a 4/3 unit difference in the fFN- group (consistent with the pro-rata rate of delivery <34 weeks), with the same 15 unit standard deviation, then the study will have 71%, 73%, and 76% power if 1125, 1200, or 1275 are randomised (375:750, 400:800; and 425:850) as per Tables 1 and 2 above. However, this is for an unadjusted analysis, and in practice we will adjust for fFN + and fFN- group, and a limited number of other baseline covariates strongly related to Bayley Score at 2 years (e.g. gender) as specified in the statistical analysis plan, and this will reduce the variability and hence increase the power. For example, if the underlying variability in the lower risk group is lower – say halved, at 7.5 units, consistent with a higher proportion having uniformly high Bayley Scores since they have no disability – then the approximate power would be 93%, 94%, and 95% respectively for 1125, 1200, or 1275 randomised in total. In practice the reduction in variability by adjusting for both this design variate (fFN + and fFN- ) and additional baseline covariates may be considerably greater, so we are confident that the original power on the childhood development outcome will be protected at or above the original 90% level by randomising at least 1125 subjects (375:750).

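### The primary obstetric and neonatal models leave out fFN status, and the article contradicts itself on whether the primary childhood analysis adjusts for it

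*Protocol article*

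**What the plan says.** **Obstetric outcome:** "The outcome is compared between the treatment groups using a logistic regression model including treatment and previous pregnancy of at least 14 weeks".

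**Neonatal outcome:** "This outcome is also compared between the treatment groups using a logistic regression model including treatment and previous pregnancy of at least 14 weeks".

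**Childhood outcome:** the primary analysis is a two-stage model, with a binomial test for deaths and a generalised linear model for survivors. Covariate-adjusted estimates are assigned to secondary analyses.

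**Appendix, childhood development outcome:** after giving unadjusted power of 71%, 73% and 76%, the text says "in practice we will adjust for fFN + and fFN- group", together with a few other baseline covariates to be named in the SAP. It calls fFN a design variate and expects power to be held at 90% or above.

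**Planned subgroup analyses:** "subgroups of the ITT population will be formed according to the following factors". The factors are reason for risk, earlier pregnancy of at least 14 weeks, cervical length and chorioamnionitis. fFN is not among them.

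**Treatment phase inclusion criteria, and the sample size section:** the trial was planned for 750 fFN-positive women. Since September 2010 it has also randomised fFN-negative women with certain risk factors, and the revised minimum is 375 fFN-positive and 750 fFN-negative.

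**The concern.** fFN status is the variable on which the revised design is built. It sets the route of entry, it splits the planned sample 1:2, and the Appendix assumes very different untreated risks on either side of it. A baseline variable of that kind normally belongs in the primary model: leaving it out gives up some power and, if randomisation is not stratified on it, leaves chance imbalance in fFN uncorrected.

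The childhood outcome has a sharper problem. Its power claim rests partly on an adjustment that the primary analysis, as described, does not make.

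The subgroup section aims to find out who responds better or worse. Two thirds of the planned sample now come from a cohort that the trial was not first designed for, yet no listed analysis estimates the effect separately in the two cohorts.

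**Working it through.** **Inputs (Appendix).**
- Two-sided 5% test: "95% power at a 5% level of significance to detect such a reduction from 40% to 27% using a two-sided binomial test".
- Equal arms: "A sample size of 750 (375 per group) gives adequate statistical power". I assume the same for the revised design.
- Sizes (fFN-positive : fFN-negative): 375:750, 400:800 and 425:850.
- Untreated delivery before 34 weeks (fFN-positive/fFN-negative): 40/10, 45/13 and 50/15%. The third pair is taken from Table 1; the text above it has 45/15. Relative reduction 32.5%.
- Untreated neonatal composite: 25/8%. Relative reduction 40%.
- Loss to follow-up: no rate is given, and I apply none.

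Assumed risk ratios between cohorts: 0.40/0.10 = 4.0; 0.45/0.13 = 3.5; 0.50/0.15 = 3.3 (0.45/0.15 = 3.0); neonatal 0.25/0.08 = 3.1.

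**Step 1: reproduce the stated power.** Pool the cohorts: p0 = (a + 2b)/3, p1 = p0(1 − r), n = N/2 per arm, p̄ = (p0 + p1)/2.

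Power = Φ{[p0 − p1 − c − 1.96·√(2p̄(1−p̄)/n)] / √([p0(1−p0) + p1(1−p1)]/n)}, with c = 1/n for continuity correction, otherwise 0.

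For 40/10 at 1125: p0 = 0.200, p1 = 0.135, n = 562.5. With correction: (0.0650 − 0.0018 − 1.96 × 0.02227)/0.02218 = 0.88, power 81.1% (stated 81%).

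| Rates | Stated, 1125/1200/1275 | With correction | Without correction |
|---|---|---|---|
| 40/10 | 81/83/85 | 81.1/83.7/85.9 | 83.2/85.5/87.5 |
| 45/13 | 88/90/92 | 88.6/90.6/92.2 | 90.0/91.7/93.2 |
| 50/15 | 93/94/95 | 92.9/94.3/95.5 | 93.8/95.1/96.1 |
| Neonatal 25/8 | 81/83/86 | 81.2/83.8/86.0 | 83.7/86.0/87.9 |

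With correction every cell is within one point. The stated powers are therefore crude pooled comparisons with no fFN term.

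**Step 2: add fFN.** Stratified (Mantel-Haenszel type) score test, with n_k per arm in stratum k:
- D = Σ(n_k/2)(p0k − p1k)
- V0 = Σ(n_k/2)²·2p̄k(1−p̄k)/n_k
- V1 = Σ(n_k/2)²[p0k(1−p0k) + p1k(1−p1k)]/n_k
- Power = Φ{(D − 1.96√V0)/√V1}

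For 40/10 at 1125: D = 93.75 × 0.130 + 187.5 × 0.0325 = 18.28, √V0 = 5.94, √V1 = 5.90. Then (18.28 − 11.64)/5.90 = 1.125, power 87.0%.

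| Rates, N = 1125 | Without fFN | With fFN | Simulated likelihood ratio test |
|---|---|---|---|
| 40/10 | 83.2 | 87.0 | 83.6 → 87.2 |
| 45/13 | 90.0 | 92.8 | 90.4 → 93.0 |
| 50/15 | 93.8 | 96.0 | 94.0 → 96.2 |
| Neonatal 25/8 | 83.7 | 85.3 | 84.6 → 85.9 |

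Both formula columns omit the continuity correction, so they compare like with like. The simulation used 40,000 trials per row, simple 1:1 randomisation, and 376 in place of 375 fFN-positive women. If randomisation were stratified by fFN, the simulated 40/10 gain would be 84.7% to 87.1%, and the unadjusted test would have a type I error of about 3.6%, against 5.1% with fFN.

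**Step 3: the childhood power claim.** Average difference (4 + 2 × 4/3)/3 = 2.22 points. With SD 15 and n = 562.5: Φ{2.22/(15·√(2/562.5)) − 1.96} = 70.0%; 72.8% and 75.3% at the larger sizes (stated 71, 73, 76). The Appendix example giving 93–95% halves the SD in fFN-negative women: √[(225 + 2 × 56.25)/3] = 10.6, which gives 94.0, 95.2 and 96.3%. That gain comes from an assumed smaller spread, so the example does not show that adjustment reaches 90%. At 1125, 90% power needs SD = 2.22 × √281.25/(1.96 + 1.28) ≈ 11.5, so the covariates would have to explain about 1 − (11.5/15)² = 41% of the variance if the SD is 15 in both cohorts.

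**Step 4: scale.** Under a constant 32.5% reduction, 45% falls to 30.4% (odds ratio 0.53) and 13% to 8.8% (odds ratio 0.64). The ratio of odds ratios is 0.83, so a logistic interaction is not null even when the relative reduction is identical.

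**The case against.** **The analysis plan could add fFN.** A detailed SAP is promised before unblinding, and the Appendix refers the further childhood covariates to it. This would answer a complaint about missing detail. But the article states the covariates of both logistic models, the place of adjustment for the childhood outcome and the subgroup list; a SAP that used fFN would change that text.

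**The Appendix promise covers the childhood score only.** This stands. A reader might infer that fFN adjustment was promised for all three outcomes and then dropped. Nothing in the obstetric or neonatal power text says so. The contradiction is confined to the childhood outcome.

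**The binary models match their power basis.** This stands too. A reader might infer that the trial is underpowered because fFN is omitted. Step 1 shows that Tables 1 and 2 never counted on it.

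**The gain is small and depends on the assumed rates.** It does. The article itself expects the fFN-negative rate to exceed 15%; at 45/20 the gain is about one point (95.4% to 96.3%). It is also tempting to say that the covariate is worth 150 more women. For the obstetric outcome that is close (87.0% against 87.5% at 40/10), but for the neonatal outcome it fails (85.3% against 87.9%).

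**An effect confined to fFN-positive women.** At 45/13, pooled power would then be 52%, against 83% in the fFN-positive stratum alone. A reader might take this contrast as the cost of the omission. It is not: the absence of effect in fFN-negative women is contrary to the article's assumption, and adjustment lifts pooled power only to 55%. An interaction test in that scenario has about 54% power (log odds ratio 0.629, standard error 0.306), and 43% at 40/10.

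**Adjustment is not free of consequences.** The odds ratio becomes conditional on fFN, and the scale issue in Step 4 needs handling. The documents also do not rank fFN against cervical length or birth history, so it cannot be called the strongest predictor.

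**Conclusion.** The point holds in a limited form. Both primary logistic models omit the variable that defines the trial's two cohorts, the subgroup list omits it too, and the article is inconsistent about whether the primary childhood analysis adjusts for it.

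The cost for the binary outcomes is modest: about 2 to 4 points of obstetric power and 1 to 2 points of neonatal power at 1125 women. This assumes the planning rates, equal arms, no loss to follow-up and the same relative reduction in both cohorts. The obstetric gain is nearer the lower end if randomisation was stratified by fFN, which the article does not say.

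The childhood inconsistency weighs more, because there the claim of at least 90% power leans on an adjustment that the described primary analysis does not contain.

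Without fFN in the subgroup list, no prespecified estimate addresses the original population. Such an estimate would have fair rather than high obstetric power: with 375 fFN-positive women, 76% for 40% to 27% and 83% for 45% to 30.4%. For the neonatal outcome it would be 68%. In the 750 fFN-negative women, obstetric power would be 36% to 52%.

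**What to change.** Before unblinding:

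1. Add fFN status (positive/negative) to the primary obstetric and neonatal logistic models, alongside the existing covariate.
2. Add it to the survivor part of the primary childhood model, and reconcile the Childhood outcome section with the Appendix so that both describe the same primary analysis. The power statement should then refer to that analysis.
3. Add fFN to the planned subgroups for all three primary outcomes, with estimates in each fFN group and a treatment-by-fFN interaction test. For the two binary outcomes, also show effects as risk ratios, and say that the interaction test has limited power.

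The cost is wording. The fFN result determines the route of entry and is known before randomisation, so no new data and no more women are needed. The price in interpretation is an odds ratio conditional on fFN, which the report should label as such.
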